### Economic challenges

From an economic standpoint, the reliance of the intervention on individual demand for new household connections could be a limiting factor, as the requested fee may not be affordable to all Uvira inhabitants. The installation of community taps partially addresses equity concerns, although the water price defined by management committees may still be a barrier to utilisation of these for those living in precarious conditions. Competition between water sales from community taps and individual household connections or use of the latter by multiple households may also affect this impact evaluation. Operational and billing information from REGIDESO will be used in complement to household surveys to better understand water access and compliance with the intervention.

### Research-specific challenges and limitations

From a research standpoint, the fact that the new tank, which is expected to improve service quality in all clusters, will be put into service half-way through cluster-level improvements (Fig. 2) and the flexible step duration (and o verlap between steps) to allow prolonged installation of new household connections—another pragmatic choice required to adapt to the context—both represent deviations from a standard SW-CRT roll-out. Likewise, the heterogeneity in cluster characteristics (Table 1), due to local constraints, is large for a SW-CRT. These aspects will be accounted for in the stepped-wedge analysis by considering potential confounders. An ITS analysis will also be conducted, which does not depend in any way on the intervention structure and implementation.

Spill-over effects could also potentially undermine the study design if inhabitants of a control cluster are able to use an improved “intervention” water service in a neighbouring cluster; for example, if a new private connection is used by multiple households. While household surveys may provide insights into the actual use of water services, we will not be able to systematically assess intervention compliance over the entire city. An intention-to-treat approach will therefore be used in the analysis and a sensitivity analysis will be performed to assess the influence of excluding participants who live within spatial buffers of different widths along the clusters’ borders. Given the predominance of within-household cholera transmission over infection from environmental sources [41, 61], we expect spill-over effects, if any, to remain of limited magnitude.

The reliance on clinical surveillance to assess cholera incidence is another limitation of this evaluation, as it may be influenced by healthcare-seeking behaviour. Although we will not be able to quantify CTC attendance rates for diarrhoeal disease symptoms across Uvira, we will seek to collect information on care habits during the household survey and critically review assumptions related to healthcare use for diarrhoeal diseases. The confirmation of cholera cases by RDTs rather than by culture or molecular methods (PCR) also responds to the need for pragmatic research approaches, as RDTs were identified as the only confirmation method that could be reliably used in the Uvira context considering available resources and laboratory capacity at the time this study started.

The Uvira Health Zone is among those identified as “hotspots” and that will be prioritised for Oral Cholera Vaccination in South Kivu as part of the national strategy to tackle cholera [62]. The deployment of a cholera vaccination campaign—or other cholera and/or COVID-19 control activities—concurrently with water supply improvements that we seek to evaluate could adversely affect our ability to attribute any observed change in cholera incidence to the water supply intervention. Furthermore, since the intervention is expected to simultaneously improve water quality and quantity, our ability to distinguish between the causal effects of these two elements through this trial if a reduction in diarrhoeal disease and/or cholera is observed will remain limited. Considering all the challenges in intervention implementation described above, there is also a possibility that no impact on trial outcomes will be detected despite the efforts deployed by the construction team to follow the study protocol and randomisation. Our hope is that the combination of multiple research and analysis methods in this research project will allow for a comprehensive, well-informed assessment of the water supply intervention and interpretation of its impacts.

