The first axis of surveillance and monitoring of cholera is often hindered by weak national health systems in those countries where cholera is endemic [6, 16–18], and there is substantial underreporting [6]. Another challenge lies in the broad criteria of the WHO’s cholera case definition [19] which defines a “suspected cholera case” in endemic areas as presentation of acute watery diarrhoea with or without vomiting. These broad clinical criteria can lead to misdiagnosis of cholera cases, and whilst WHO recommends laboratory confirmation, suspected cases are not consistently confirmed by laboratory methods [18]. Studies from several African countries [20–22] and from Haiti [23, 24] found laboratory confirmation by culture of between 0 and 63% of suspected cholera cases.

The second axis, vaccination campaigns, is supported by oral cholera vaccines (OCV) which can provide protection against cholera for 2 to 4 years [25, 26] and indirect protection via herd immunity has also been documented [27–30]. A global stockpile was created in 2013 to ensure OCV availability for cholera control in outbreaks and humanitarian emergencies [31]. As OCV supply capacity increased in recent years, mass vaccination campaigns in transmission hotspots, in conjunction with improvements in WASH services, are now the foundation of the GTFCC strategy to eliminate cholera along with effective surveillance [15].

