Since 2012, the Agence Française de Développement (AFD) and the Veolia Foundation (VF), with support from the European Union, have invested approximately 13 million euros in improvements to the water supply infrastructure in Uvira (Democratic Republic of the Congo, DRC), an identified hotspot for cholera transmission [14]. They commissioned an independent evaluation of the health impact of the planned works. This project offered a rare opportunity to investigate how improvements in urban water supply infrastructure, in a conflict-affected, cholera-endemic area, influence the incidence of cholera and other diarrhoeal diseases. In light of the potential public health value of such research but with consideration of the multiple challenges for implementation in this setting, we employed a deliberately pragmatic approach to this study protocol. The aim of this study is to evaluate the impacts of water supply infrastructure improvements on cholera and other diarrhoeal diseases in Uvira (DRC). We have identified a number of potential risks to the study and then pre-specified mitigative measures that would permit the assessment of health impact under different scenarios. This protocol and analysis plan are shared here in accordance with best practice principle for pre-specification but also to stimulate debate in the global health sector on strategies for undertaking rigorous research in unstable settings.

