### Participants

The population of interest is all inhabitants of Uvira, assuming that all Uvira inhabitants affected by severe diarrhoeal disease or cholera will eventually seek care or be referred to the CTC. All patients admitted to the CTC with suspected cholera are eligible for participation in the study and collection of a rectal swab for cholera confirmation (Fig. 2). No restriction is placed on patient age.

Following approval by the Ministry of Health for DRC, the CTC Coordinator can extract and share anonymised patient information as recorded in the CTC registry, including age, sex, address, dates and length of stay, and antibiotic treatment if any. All information that is extracted and included in this study protocol is anonymised with no personal identifiers included. Aggregated census data provided by municipal authorities will be used to estimate the population size for each cluster.

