As a complement to the main stepped-wedge analysis, an additional analysis will be carried out which makes fewer assumptions about the structure of the intervention. An interrupted time series analysis will be fitted using historical data, with a fixed starting point for the intervention rather than staggered starting points as assumed in the analysis above. Data collected throughout the intervention until completion of the works in the last cluster will be excluded from the analysis. We intend to continue data collection for at least 12 months after completion of the intervention to allow comparison of suspected and confirmed cholera incidence before and after water service improvements.

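### A cholera vaccination campaign is foreseen as a threat to attribution, but the article names no vaccination data, model term or interpretation rule; under the stated models a campaign during roll-out would be read as a water effect

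*Protocol article*

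**What the plan says.** The Introduction of the protocol article undertakes to pair the identified risks with "pre-specified mitigative measures that would permit the assessment of health impact under different scenarios", and the Abstract makes a similar promise.

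Under Research-specific challenges and limitations, the Uvira Health Zone is listed among those that "will be prioritised for Oral Cholera Vaccination in South Kivu as part of the national strategy to tackle cholera". The same paragraph accepts that a campaign running alongside the works "could adversely affect our ability to attribute any observed change in cholera incidence to the water supply intervention". The only response is general: "Our hope is that the combination of multiple research and analysis methods in this research project will allow for a comprehensive, well-informed assessment".

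On data, the Participants section describes registry information "including age, sex, address, dates and length of stay, and antibiotic treatment if any". Trial data collection, the household survey and the candidate confounders in the Analysis plan do not mention vaccination either.

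On models, the Analysis plan gives a Poisson GEE in which time enters through a harmonic term. No step or calendar-period effect is stated. The ITS has one fixed start, leaves out all data from the roll-out until works finish in the last cluster, and then compares before with after: "We intend to continue data collection for at least 12 months after completion of the intervention". The Introduction says that OCV "can provide protection against cholera for 2 to 4 years".

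**The concern.** Both primary outcomes, suspected and confirmed cholera, respond to OCV. A campaign during the works lowers incidence later in calendar time, which is also when more clusters have the intervention. If nothing in the model represents vaccination or non-seasonal time, the water coefficient absorbs the fall.

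Other threats get a concrete response in the article. Departure from the allocation leads to confounder adjustment and a non-randomised analysis, spill-over to a buffer sensitivity analysis, and care-seeking to survey questions. Vaccination gets none. At stake is whether a reported reduction could be credited to the water supply at all. The ITS, offered as the fallback because it does not rely on the roll-out structure, is also exposed.

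**Working it through.** **Plan's own figures.** Table 1 gives 105.6 suspected cases per month over a summed population of 260,962, so 105.6 / 260,962 = 0.405 per 1000. This agrees with the stated 0.4. The stepped-wedge minimum detectable difference is 0.1 / 0.4 = 25%, a rate ratio of 0.75. The ITS minimum detectable reduction is 65% (12 months) or 75% (6 months). The point itself rests on no stated figure.

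**Assumed campaign effect (not in the documents).** Effect = coverage x protection. For example, 0.50 x 0.60 = 30%, with a range from 0.30 x 0.60 = 18% to 0.80 x 0.60 = 48%.

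**Stepped wedge.** Noise-free expected counts were built from Table 1 (case means, populations, allocation sequence; South = sequences 1-6) with a true water rate ratio of 1:

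E(Y) = baseline cases in the cluster x (1 - r x V),

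where V = 1 in vaccinated clusters from step 4 and r = 0.30 or 0.50. Layout assumed: 4-week periods, 3 before, 16 steps, 3 after, and 2 transition periods excluded per cluster. The fitted model was Poisson with a population offset, cluster effects (standing in for the GEE), a binary water indicator and the stated time term. Water rate ratios for r = 0.30 / 0.50:

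| Campaign | Harmonic only (as stated) | Period effects (not stated) | Harmonic + OCV term |
|---|---|---|---|
| City-wide | 0.79 / 0.62 | 1.00 / 1.00 | 1.00 |
| South only | 0.86 / 0.76 | 0.87 / 0.76 | 1.00 |
| North only | 0.95 / 0.91 | 1.15 / 1.33 | 1.00 |

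With period effects plus an OCV term, the two partial campaigns also return 1.00. A city-wide step is already absorbed by the periods.

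Varying the start of the campaign within the roll-out, with monthly steps and a 30% effect, the harmonic model gives 0.73-0.80 city-wide and 0.84-0.95 for partial campaigns. At 18% the values are 0.84-0.88 and 0.90-0.97; at 48% they are 0.56-0.68 and 0.74-0.92. All lie below 1. The city-wide values at 30% correspond to apparent reductions of 20-27%, next to the 25% the trial is sized for.

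**Suspected cases.** Only their cholera fraction responds. With an assumed fraction of 40-60%, a 30% effect on cholera becomes 0.30 x 0.4 = 12% to 0.30 x 0.6 = 18% on suspected cases, so the bias there is nearer the 18% values.

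**ITS.** Poisson with trend, harmonics and one level change; assumed 132 months before, 24 excluded and 12 after.

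- *City-wide campaign in the excluded window or at its end.* Protection of 2 to 4 years covers the 12-month post-period when the campaign falls late enough in the roll-out, which the Analysis plan puts at under 2 years. Holding protection constant, the vaccine and post-intervention indicators are then identical in the analysed data (design rank 5 of 6). The rate ratio with no water effect is 1 - 0.30 = 0.70 (0.82 to 0.52 over the 18-48% range).
- *Campaign starting 4 to 7 months into the post-period.* The bias at 30% is smaller (0.82 to 0.90). The two indicators are separable (rank 6 of 6) from the campaign date alone.

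**The case against.** The strongest reply is that the threat is disclosed and conditional. The article says the zone will be prioritised, gives no date, and raises a concurrent campaign only as a possibility. It is also a condensed article whose field lists are open-ended, and the analysis plan is not shown. This stands in part: a reader might infer that the trial collects no vaccination data, but the document supports only that none is named. It does not remove the point, because disclosure is not the mitigation promised, and the models as stated would misattribute a campaign's effect.

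Three further inferences are tempting and not supported:

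- *That the stepped wedge is at risk only if some clusters are vaccinated, and in either direction.* Both hold for a model with period effects, which the plan does not state. Under the stated harmonic, a city-wide campaign biases the result too, and every scenario run biases it downward.
- *That better exposure data would rescue the ITS.* For a city-wide campaign in the excluded window it would not. For one starting in the post-period, the date is enough.
- *That the exposure could never be reconstructed.* The Ministry of Health and cholera response organisations sit on the steering committee, and nothing suggests that campaign records would be unavailable later.

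It is also fair that the ITS is a complement, and that a 30% artefact lies well below its 65-75% detectable reduction. The 25% benchmark belongs to the stepped wedge. The ITS point estimate would still be shifted by the full campaign effect.

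**Conclusion.** The point holds in a limited form. The article foresees OCV, admits that a concurrent campaign could harm attribution, and names no data, model term or interpretation rule for it, despite promising mitigation. If a campaign occurs during roll-out, the stated stepped-wedge model biases the water rate ratio downward: about 0.79 city-wide, 0.86 South-only and 0.95 North-only for a 30% effect from step 4. A city-wide campaign in the ITS's excluded window cannot be separated from the water works.

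These sizes rest on assumed coverage, protection and timing, a binary water indicator, cluster effects in place of the GEE, and the assumed step layout. Bias in suspected cases is smaller, in proportion to their cholera fraction. If no campaign takes place, there is no bias from this source. The change is worth making because it is cheap and easiest to prespecify before any campaign.

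**What to change.** 1. Obtain OCV campaign dates, areas and doses from the health authorities on the steering committee, and derive coverage by cluster and month. An OCV question on the patient form and in the household survey is supplementary only: patient status describes cases rather than the population, and 500 households over 16 clusters (about 31 each), surveyed once after completion, cannot give cluster-month coverage.
2. Prespecify cluster-month OCV coverage as a time-varying term in the stepped-wedge model for both primary outcomes, or as a sensitivity analysis together with calendar-period effects.
3. State that, if a campaign falls in the ITS's excluded window, the ITS estimate will be reported as the combined effect of water and vaccine. Any offset sensitivity analysis should apply log(1 - coverage x protection), over a stated range of protection, to confirmed cases only. For suspected cases it should be scaled by the cholera fraction, since the unscaled offset over-corrects. A campaign starting within the post-period can be modelled from its date.

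Cost: one data request, one covariate and, if a campaign occurs, a wider stepped-wedge standard error. Under the harmonic model the increase is roughly 6-30% for a partial campaign and about 50% for a city-wide one. With period effects and a partial campaign, examples are 0.100 to 0.108 (8%) and 0.109 to 0.123 (13%) on the log scale.

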## Conclusion

Overall, the Uvira trial is expected to generate new evidence on the impact of large-scale improvements in piped water service in a conflict-affected cholera transmission hotspot. A pragmatic approach is presented in this protocol that should enable conduct of the research in a challenging context without undermining the scientific validity of the trial.

## World Health Organization Trial Registration Data Set

**Table Taba:** 

#	Item	Description
1	Primary Registry and Trial Identifying Number	*clinicaltrials.gov*, NCT02928341
2	Date of Registration in Primary Registry	10th October 2016
3	Secondary Identifying Numbers	LSHTM Ethics Review Board protocols #8913, #10603
4	Source(s) of Monetary or Material Support	French Agency for Development (AFD) Veolia Foundation (VF)
5	Primary Sponsor	London School of Hygiene and Tropical Medicine (LSHTM)
6	Secondary Sponsor(s)	None
7	Contact for Public Queries	[name], Principal Investigator, [contact] [name] [name]
8	Contact for Scientific Queries	
9	Public Title	Impact Evaluation of Urban Water Supply Improvements on Cholera and Other Diarrhoeal Diseases in Uvira, Democratic Republic of Congo
10	Scientific Title	The impact of improved water supply on cholera and diarrhoeal diseases in Uvira, Democratic Republic of the Congo: a pragmatic stepped-wedge cluster randomised trial and economic evaluation
11	Country of Recruitment	Democratic Republic of the Congo
12	Health Condition(s) or Problem(s) Studied	Cholera, diarrhoeal disease
13	Intervention	Control: current water supply service Intervention: improved water supply service (new and rehabilitated supply network infrastructure including community and household tap connections)
14	Key Inclusion and Exclusion Criteria	Inclusion Criteria: Uvira resident (without restriction placed on age or sex) admitted to the Uvira Cholera Treatment Centre at the General Hospital in Uvira Exclusion Criteria: Any patients admitted during the period of intervention implementation in each cluster
15	Study Type	Interventional; stepped-wedge cluster randomised trial
16	Date of First Enrolment	10th October 2016
17	Sample Size	Planned enrolment: 5000 Enrolment to date: 4280
18	Recruitment Status	Recruiting
19	Primary Outcome(s)	(1) monthly incidence of suspected cholera cases, as measured by the number of CTC admissions attributed to each cluster; (2) monthly incidence of confirmed cholera cases, based on rapid detection test (RDT) results for consenting patients
20	Key Secondary Outcomes	None
21	Ethics Review	Approved. LSHTM Ethics Committee: #8913, 14th December 2015; #10603, 7th April 2016 Kinshasa School of Public Health Ethics Committee: ESP/CE/088/2015, 4th September 2015 (last renewal: ESP/CE/143/2020, 23rd August 2020)
22	Completion Date	Expected 27th September 2021
23	Summary Results	Not available
24	IPD Sharing Statement	No IPD sharing

## Data Availability

Any use of trial data will be controlled by the Principal Investigators. All final, anonymised datasets and statistical analysis codes will be made available on a public repository (e.g. Open Science Framework, osf.io) at the time of publication of trial results.

## Abbreviations

AFD: Agence Française de Développement
CBA: Cost-benefit analysis
CEA: Cost-effectiveness analysis
CONSORT: Consolidated Standards of Reporting Trials
CTC: Cholera Treatment Centre
DALY: Disability-adjusted life years
DRC: Democratic Republic of the Congo
ETEC: Enterotoxigenic *Escherichia coli*
GEE: Generalised estimating equations
GPS: Global Positioning System
GTFCC: Global Task Force on Cholera Control
ICC: Intraclass correlation coefficient
ITS: Interrupted time series
LSHTM: London School of Hygiene and Tropical Medicine
MDD: Minimum detectable difference
NGO: Non-governmental organisation
OCV: Oral cholera vaccine
RDT: Rapid detection test
SDG: Sustainable Development Goals
SW-CRT: Stepped-Wedge Cluster Randomised Trial
VF: Veolia Foundation
WASH: Water, sanitation and hygiene
WHO: World Health Organization
